### Study procedures

#### Pre-intervention assessments (T0)

After signing consent, participants will complete the baseline questionnaire (T0), online or on paper. Sections include demographics, fatigue, quality of life and self-efficacy. See 'participant psychosocial measures' section below. After submitting the T0 questionnaire, all participants will receive the REFRESH self-help booklet in hard copy (given in person or sent in the mail) and commence STEP 1. Figure 2 depicts study procedures.

**Fig. 2 Fig2:**
[figure not shown]
Model of REFRESH: finding new energy after cancer stepped care

#### STEP 1: Supported self-management and REFRESH self-help booklet

The REFRESH self-help booklet was developed by experienced health professionals and researchers based on existing literature. A multidisciplinary panel of experts, consumers, health literacy specialists and professional graphic designers contributed to refine and produce the REFRESH booklet. The self-help booklet is structured into five chapters (see Table 1). Participants will be encouraged to read and complete the activities of one chapter per week, for 5 weeks. Each week participants will be contacted by a study psychologist both via email (weeks 1, 3 and 4) and via telephone (weeks 2 and 5). The purpose of these weekly contacts is to discuss and support participation, answer questions and troubleshoot problems. If participants miss a chapter, they will be encouraged to proceed with the next chapter and take note of any sections they feel are relevant to them from the preceding chapter. Each week, they will also complete some feedback questions pertaining to the chapter completed/attempted.

**Table 1 Tab1:** REFRESH session goals and objectives

STEP 1—chapter #	STEP 2-session #	Session topic	Session goals and objectives
1	n/a	Understanding fatigue	To provide information and psycho-education about cancer-related fatigue including medical and psychosocial causes of CRF, and explanation of CBT and its role in CRF. Introduction to an activity diary for tracking fatigue
2	**1**	Understanding feelings	To understand the impact of emotions on fatigue and strategies to increase pleasant emotions. Introduction to relaxation strategies (breathing, muscle relaxation and mindfulness)
3	**2**	Helpful behaviours	To understand the role of behaviours in impacting fatigue. Mood monitoring, increasing physical activity, pacing and scheduling pleasant and mastery activities for the week ahead as part of behavioural activation
4	**3**	Adaptive thinking	To understand the role of cognitions in influencing emotions, behaviour and fatigue. Identifying unhelpful thoughts and ‘thinking traps’, cognitive restructuring via use of a thought diary. Introduction to worry postponement strategy and coping statements
5	**4**	Moving on	Summarise skills learnt and identify which are helpful and can be implemented ongoing. Assistance with developing a coping card if this hasn’t been done prior. Assistance with identifying additional supports. Assistance with accessing further professional supports if needed

As a contingency, participants who are too distressed or unable to engage with the self-help program within two weeks after commencing STEP 1 can be fast tracked to STEP 2 (see below).

#### Time 1 assessments (T1)

After 5 weeks, participants will complete a follow-up questionnaire. The T1 questionnaire includes fatigue, quality of life and self-efficacy questions (repeated T0 measures), in addition to feasibility and satisfaction measures (see “study measures” below).

#### Eligibility for STEP 2

Eligibility for STEP 2 is based on a participant’s change in fatigue scores following STEP 1. Fatigue will be measured using the Functional Assessment of Chronic Illness Therapy—fatigue subscale (FACIT-F) scores [22]. Participants with a T1 FACIT-F score greater than 34 or at least 10 points greater than T0 will be encouraged to continue their strategies without further CBT intervention. Participants with a FACIT-F score on the T1 questionnaire below 34 (severe) or less than 10 points greater than T0 will be considered for STEP 2 in conjunction with a psychologist’s clinical judgement of further support needs.

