**Method/design:**

This is a single-arm feasibility study. Fifty people with a cancer diagnosis, at least 12 weeks post-treatment or on long-term maintenance treatment, with persistent CRF that is affecting daily activities, will enrol in a stepped-care CBT program. Intervention: The stepped-care program involves two steps. Step 1: All participants begin with a 5-week supported self-management CBT progam targeting fatigue. Step 2: If fatigue remains severe or has changed less than the minimal clinically important difference on the fatigue measure after step 1, participants will be offered four sessions of therapist-directed group CBT. Measures: Participants will complete questionnaires at baseline and 6 and 10 weeks. The primary outcome is feasibility of the REFRESH program. The implementation evaluation comprises acceptability, satisfaction, appropriateness, and feasibility of the study intervention, along with administrative data including cost, processes, procedures and implementation. Secondary outcomes are changes in fatigue, quality of life and self-efficacy.

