### Implementation outcome measures

The implementation evaluation plan is guided by the Medical Research Council (MRC) framework for conducting and reporting process evaluations [23]. This means that rather than focussing on intervention effects (which assume adequate sample size, randomisation etc.), the focus is on understanding *how* interventions work in practice and the mechanisms for behaviour change. Therefore, there is more emphasis on factors such as whether participants were able to work through the self-help booklet, rather than focussing solely on changes to outcome measures. This approach assists evaluators to decide aspects of the intervention or its context to prioritise for further investigation or clinical implementation. The implementation evaluation includes acceptability, satisfaction, appropriateness, feasibility of the stepped-care intervention, recruitment, retention, adherence, cost and fidelity. Table 2 summarises the evaluation processes and measures.

**Table 2 Tab2:** REFRESH evaluation plan and measures

Implementation outcomes	Definition	Rationale	Method of evaluation
**Acceptability and Satisfaction**	The perception amongst users that the program is palatable and satisfactory [24]	Users consider the program acceptable	**□ The Acceptability of Intervention Measure (AIM)**^a^ **□ Client Satisfaction Questionnaire (CSQ)**^b^ **□** Recruitment and withdrawal records **□** Open-ended study-devised questionnaire items (e.g. perceived barriers and/or helpfulness of chapters)
**Appropriateness**	The perceived fit and relevance of the program to users [24], indicated by proportion of people willing to try and complete the program	Consumers perceive it is worth trying and completing the program	**□ The Intervention Appropriateness Measure (IAM)**^a^ **□** Retention (proportion of enrolled participants who completed follow-up assessments; proportion of participants who completed each module of step 1; proportion of participants who completed step 2) **□** Adherence to step 1 and step 2 (percentage of sessions attended, reasons for not completing sessions, number of days overdue for completed questionnaires).

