**Feasibility of materials and CBT group attendance**	The extent to which stepped care approach to CBT can be used for cancer fatigue	A majority of participants complete step 1 in 6 weeks and/or step 2 in 4 sessions	**□ The Feasibility of Intervention Measure (FIM)**^a^ **□** Open-ended study-devised questionnaire items (e.g. number of chapters of the self-management booklet attempted/completed)
**Cost**	The resource cost of delivering the program per user	This self-help CBT program is expected to provide therapy at a lower cost compared to face to face, enabling more users to benefit	**□** Booklet cost and records of therapist/administration time per person enrolled **□** Proportion of participants requiring step 2
**Fidelity**	The degree to which the program was implemented as intended [24]	The adherence and deviations to program contacts and stepped care protocol	**□** Field notes maintained by researchers **□** Session checklist after each STEP 2 session to ensure all topics covered

^a^The AIM, IAM and FIM are 4-item (each) validated measures with items rated on a 5-point Likert scale from ’completely disagree’ to ‘completely agree’ with higher scores indicating greater intervention acceptability, appropriateness and feasibility respectively [25]

^b^The CSQ [26] is a well validated 8-item measure of the quality of the intervention, the extent to which the program met participant’s needs, perceived increases in skills and whether participants would recommend the program to others. Total scores range from 8 to 56, with higher scores indicating greater satisfaction

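### The exit rule and the STEP 2 rule overlap, and the article does not say which prevails for a participant who meets both

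*Protocol article*

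**What the plan says.** The Eligibility for STEP 2 text, under Time 1 assessments (T1), opens by basing eligibility on a participant's "change in fatigue scores following STEP 1". Two sentences then divide the participants.

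- **Exit:** "Participants with a T1 FACIT-F score greater than 34 or at least 10 points greater than T0 will be encouraged to continue" with their strategies and no further CBT.
- **STEP 2:** those with a T1 score "below 34 (severe) or less than 10 points greater than T0 will be considered for STEP 2", together with a psychologist's judgement of support needs.

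The abstract (Method/design) restates only the second rule: "If fatigue remains severe or has changed less than the minimal clinically important difference on the fatigue measure after step 1", the participant is offered group CBT.

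The FACIT-Fatigue section supplies the scale. Scores run from 0 to 52, lower is worse, below 34 is severe, and a 10-point improvement is clinically important.

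Table 2 lists measures that depend on who goes to STEP 2. Under Cost it has "Proportion of participants requiring step 2"; under Appropriateness, "proportion of participants who completed step 2"; under Fidelity, "The adherence and deviations to program contacts and stepped care protocol", recorded through "Field notes maintained by researchers". The Data analysis section describes change from baseline separately for STEP 1-only participants and for those who took both steps.

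**The concern.** The complement of an either-or condition is a both-and condition. Here the two sentences meant to split participants are both either-or, so some people satisfy each of them. They are those who ended above the severity cut with a small gain, and those who gained 10 points or more but are still severe. Many are partial responders, the people a stepped-care rule exists to sort.

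The exit sentence carries no clinical discretion. The psychologist's judgement is attached only to the STEP 2 sentence, so it does not say which sentence governs a participant who meets both.

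The rule determines who is considered for STEP 2 after T1. It therefore shapes the proportion requiring STEP 2 and what counts as a departure from the stepped-care protocol. Through who is offered STEP 2, it also affects the group over which STEP 2 completion is reported and the make-up of the two groups in the change analysis. The Discussion ties each STEP 2 participant to an extra 4 hours of therapist time, so the cost result depends on which reading was used. The AIM, IAM, FIM, CSQ and recruitment results are not computed from this rule.

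**Working it through.** **Inputs.** From Eligibility for STEP 2, with gain = T1 − T0:

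- Exit: T1 > 34 or gain ≥ 10.
- STEP 2: T1 < 34 or gain < 10.

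From FACIT-Fatigue: integer scores 0 to 52, so 53 × 53 = 2,809 (T0, T1) pairs. The article states no figure of its own to reproduce.

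**Classification of all pairs.**

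| Result | Pairs |
|---|---|
| Both rules: T1 > 34, gain < 10 | 333 |
| Both rules: T1 < 34, gain ≥ 10 | 300 |
| Exit only | 646 |
| STEP 2 only | 1,530 |
| Neither | 0 |
| Total | 2,809 |

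Overlap: 333 + 300 = 633.

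**Check by baseline score.**

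- T0 = 0 to 23: overlap for T1 from T0 + 10 to 33, giving 24 + 23 + … + 1 = 300.
- T0 = 24 and 25: no overlap.
- T0 = 26 to 43: overlap for T1 from 35 to T0 + 9, giving 1 + 2 + … + 18 = 171.
- T0 = 44 to 52: overlap for T1 from 35 to 52, giving 9 × 18 = 162.
- 171 + 162 = 333. Baseline scores with some overlap: 24 + 27 = 51 of 53.

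**Severe at baseline (T0 < 34).** 34 × 53 = 1,802 pairs, of which 300 + 36 = 336 meet both rules. All 336 are improvements; the smallest is 2 points (33 to 35). The other 633 − 336 = 297 overlap pairs have T0 of 34 or more. Such baselines are possible because entry is by a 0–10 rating and symptom descriptors, not by FACIT-F.

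**T1 exactly 34.** Neither cut names this score, so gain alone decides: 25 pairs exit (for example 24 to 34) and 28 go to STEP 2 (for example 25 to 34). It is not part of the overlap.

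**Testing the repairs.**

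| Rule | Exit | Considered for STEP 2 | Both | Neither |
|---|---|---|---|---|
| (a) Exit if T1 ≥ 34 and gain ≥ 10 | 646 | 2,163 | 0 | 0 |
| (b) STEP 2 if T1 < 34 and gain < 10 | 1,307 | 1,502 | 0 | 0 |

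The two differ on 2,163 − 1,502 = 661 pairs: the 633 overlap pairs plus the 28 with T1 = 34 and gain < 10. Changing or to and in the exit sentence while keeping a strict > 34 would leave the 25 pairs with T1 = 34 and gain ≥ 10 in neither group.

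**Illustration in participants (assumed values, not from the article).** T0 is taken as normal with mean 22, 26 or 30 and SD 9, and change as normal with mean 3, 6 or 9 and SD 8, rounded and held to 0–52. Over these nine scenarios, about 9 to 17 of 50 participants would meet both rules. The share considered for STEP 2 would be 62–88% under (a) and 27–68% under (b). Within a scenario the two differ by 20 percentage points (87.8 − 67.8) to 36 (73.7 − 37.5).

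**The case against.** The strongest reply is that the abstract settles the matter. It repeats the STEP 2 rule with its either-or, so two statements agree and only the exit sentence is out of line; one word was probably mistyped. That lean is real and is a good reason to prefer repair (a). It does not cancel the exit sentence, though. The eligibility text itself starts from change in fatigue, and the Discussion judges STEP 1 by clinically meaningful improvement. Both sit awkwardly with sending someone who moved from 18 to 30 onward as a matter of rule.

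Second, neither sentence is a binding allocation: one group is encouraged, the other considered, and a psychologist decides. This stands, and it limits the harm. It does not tell the psychologist whether a participant who meets both is theirs to consider.

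Third, the downstream analyses are descriptive, and the change groups are defined by what participants actually took up. That is correct. Those groups stay well defined, but their make-up still reflects whichever reading was applied. That STEP 2 completion is counted over those offered STEP 2 is an inference; Table 2 names no denominator.

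Fourth, counts of score pairs carry no probability weight, and nearly half of the overlap (297 of 633) has a baseline that is not severe. This also stands; the counts show that the conflict is not a corner case, not how many people it affects.

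Finally, distressed participants or those unable to engage can be fast-tracked to STEP 2 before T1. That is a separate route and does not resolve the overlap. Fig. 2 and the full protocol are not shown and may hold an operational rule, but that would not make the two published sentences compatible.

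**Conclusion.** The concern holds and should be fixed. As written, the two sentences give incompatible instructions for 633 of 2,809 score pairs, at 51 of 53 baseline scores, with no precedence. This follows from the wording and the 0–52 range alone and needs no distributional assumption. The number of participants affected cannot be derived from the article; the 9 to 17 of 50 shown above depends wholly on assumed means and SDs.

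The consequence is bounded. The proportion requiring STEP 2 and the fidelity assessment lack a defined reference rule, and a reader cannot tell which rule produced the result. The questionnaire-based implementation outcomes are untouched. The finding is confined to the article text.

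**What to change.** Keep one rule and make the other its exact complement. Assign T1 = 34 to the not-severe side, since the FACIT-Fatigue section calls only scores below 34 severe.

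**(a) Fewest changes.** Reword the exit sentence so that participants stop after STEP 1 only if T1 is 34 or higher and at least 10 points above T0; everyone else is considered for STEP 2 with the psychologist's judgement. This changes one sentence and matches the abstract. A clause sending anyone who meets both rules to the psychologist would give the same division (1,530 + 633 = 2,163 considered). The price is a larger STEP 2 pool: someone moving from 40 to 46 is flagged, and so is everyone with T0 of 43 or more, because the largest possible gain from 43 is 52 − 43 = 9.

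**(b) Improvement-led.** Consider for STEP 2 only those with T1 below 34 and a gain under 10; all others exit, with the exit cut moved to 34 or above. This changes both eligibility sentences and the abstract clause. It lets someone exit still severe (10 to 20), or after a 1-point gain (33 to 34).

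The choice is clinical and belongs to the investigators. Either way, say that the rule applies at T1 and leaves the fast-track route as it is. No extra data are needed, since FACIT-F is already collected at T0 and T1.

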#### STEP 2: Individual or group CBT delivered by a clinical psychologist

STEP 2 participants will be offered small group CBT therapy (maximum *n* = 5 per group). Therapy will comprise up to four 50-min sessions with a clinical psychologist either face-to-face or via telehealth. Clinical psychologists in Australia have a minimum of 6 years university-level training with an additional 2 years of supervised practice. The mode of delivery (i.e. telehealth vs face-to-face) will be decided based on COVID-19 restrictions (e.g. face-to-face groups may be prohibited with statewide laws) and participant circumstances (e.g. location of participant is rural and lengthy travel time would prohibit participation). Individual sessions will be offered to those where group therapy is not appropriate (e.g. due to extensive work or parenting commitments). Sessions will be based on content in chapters 2–5 of the self-help booklet (see Table 1) and tailored to the group based on their particular concerns and areas of need. A therapist manual has been developed to assist facilitation and delivery consistency. Face-to-face sessions will be held in a clinic room at Peter MacCallum Cancer Centre.

#### Time 2 assessments (T2)

At 10 weeks post T0 (for STEP 1 only completers) or at the completion of STEP 2, all participants will complete a final T2 questionnaire. Completion of the T2 questionnaire marks the end of participation in the REFRESH study.

### Outcome measures

Measures are summarised as (1) implementation outcome measures and (2) participant psychosocial measures.

### Implementation outcome measures

The implementation evaluation plan is guided by the Medical Research Council (MRC) framework for conducting and reporting process evaluations [23]. This means that rather than focussing on intervention effects (which assume adequate sample size, randomisation etc.), the focus is on understanding *how* interventions work in practice and the mechanisms for behaviour change. Therefore, there is more emphasis on factors such as whether participants were able to work through the self-help booklet, rather than focussing solely on changes to outcome measures. This approach assists evaluators to decide aspects of the intervention or its context to prioritise for further investigation or clinical implementation. The implementation evaluation includes acceptability, satisfaction, appropriateness, feasibility of the stepped-care intervention, recruitment, retention, adherence, cost and fidelity. Table 2 summarises the evaluation processes and measures.

**Table 2 Tab2:** REFRESH evaluation plan and measures

Implementation outcomes	Definition	Rationale	Method of evaluation
**Acceptability and Satisfaction**	The perception amongst users that the program is palatable and satisfactory [24]	Users consider the program acceptable	**□ The Acceptability of Intervention Measure (AIM)**^a^ **□ Client Satisfaction Questionnaire (CSQ)**^b^ **□** Recruitment and withdrawal records **□** Open-ended study-devised questionnaire items (e.g. perceived barriers and/or helpfulness of chapters)
**Appropriateness**	The perceived fit and relevance of the program to users [24], indicated by proportion of people willing to try and complete the program	Consumers perceive it is worth trying and completing the program	**□ The Intervention Appropriateness Measure (IAM)**^a^ **□** Retention (proportion of enrolled participants who completed follow-up assessments; proportion of participants who completed each module of step 1; proportion of participants who completed step 2) **□** Adherence to step 1 and step 2 (percentage of sessions attended, reasons for not completing sessions, number of days overdue for completed questionnaires).
**Feasibility of materials and CBT group attendance**	The extent to which stepped care approach to CBT can be used for cancer fatigue	A majority of participants complete step 1 in 6 weeks and/or step 2 in 4 sessions	**□ The Feasibility of Intervention Measure (FIM)**^a^ **□** Open-ended study-devised questionnaire items (e.g. number of chapters of the self-management booklet attempted/completed)
**Cost**	The resource cost of delivering the program per user	This self-help CBT program is expected to provide therapy at a lower cost compared to face to face, enabling more users to benefit	**□** Booklet cost and records of therapist/administration time per person enrolled **□** Proportion of participants requiring step 2
**Fidelity**	The degree to which the program was implemented as intended [24]	The adherence and deviations to program contacts and stepped care protocol	**□** Field notes maintained by researchers **□** Session checklist after each STEP 2 session to ensure all topics covered

^a^The AIM, IAM and FIM are 4-item (each) validated measures with items rated on a 5-point Likert scale from ’completely disagree’ to ‘completely agree’ with higher scores indicating greater intervention acceptability, appropriateness and feasibility respectively [25]

^b^The CSQ [26] is a well validated 8-item measure of the quality of the intervention, the extent to which the program met participant’s needs, perceived increases in skills and whether participants would recommend the program to others. Total scores range from 8 to 56, with higher scores indicating greater satisfaction

### Participant details and psychosocial measures

#### Patient demographic and medical data

Sociodemographic characteristics will be collected on enrolment to gather descriptive information about which participants were drawn to and retained in the study: diagnosis and treatment details, age, sex, country of birth, language spoken, education, marital status and employment status.

#### FACIT-Fatigue (Functional Assessment of Chronic Illness Therapy—Fatigue subscale)

The FACIT-F is a valid measure of the severity of cancer-related fatigue, with a recall period of 7 days [22]. FACIT-F is a 13-item scale, with items rated on a 5-point Likert scale from 0 (not at all) to 4 (very much). Score range is 0–52, with the population mean of 43 [27]. Lower scores on the FACIT-F indicate greater fatigue and impairment. A FACIT-F score below 34 is considered to be severe [28] and a 10-point improvement a clinically important difference [29].

